**Fig. 2 Fig2:**
[figure not shown]
The secondary endpoints are illustrated. **a** Dimensions of a wart are the product of the largest diameter (mm) on an axis line (AL) of the wart and the largest diameter on a normal line of the AL. **b** The cross-sectional area of a wart is calculated from the pixel count of the digital image. **c** The number of clots observable through the surface of a wart is counted

The dimensions of a wart in this study are defined by the product of the largest diameter (mm) on an axis line (AL) of the wart and the largest diameter on a normal line of the AL (Fig. 2a). Thus:

Change in dimensions = (dimensions of the wart on a subsequent day (mm^2^)) / (dimensions of the wart on day 1 (mm^2^)) × 100 (%).

The CSA is an area (mm^2^) of the target wart that can be calculated by correcting the pixel count of a circumscribed area on a digital image (Fig. 2b). As this is a single-blind study, the area is analyzed using ImageJ by two dermatologists in hospitals other than the institutional sites who are not aware if patients are in the FIT039 or placebo group. Thus:

Change in CSA = (CSA of the wart on a subsequent day (mm^2^)) / (CSA of the wart on day 1 (mm^2^)) × 100 (%).

The change in the number of clots is defined by the change in the number of small blood clots within the area of the wart lesion in some warts, especially of the palmer and plantar type (Fig. 2c). The number of clots will be counted manually by the two dermatologists who are not aware if the patients are in the FIT039 or placebo group. Thus:

Change in clots = (number of clots on a subsequent day) / (number of clots on day 1) × 100 (%).

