### Eligibility criteria

#### Inclusion criteria

Men and women who meet the following criteria will be included: 1) having verruca vulgaris measuring 4 to 10 mm on the major axis on the extremities, including the palms and soles; 2) aged over 20 years old at the time of consent; 3) a blood test within 4 weeks prior to the registration fulfills all of the following: hemoglobin level ≥ 10 g/dL, white blood cell count ≥ 2000/μL, platelet count ≥ 100,000/μL, aspartate aminotransferase ≤ 100 IU/L, alanine aminotransferase ≤ 100 IU/L, total bilirubin ≤ 2.0 mg/dL, and serum creatinine ≤ 2.0 mg/dL; 4) all men have agreed to use proper contraception during the entire FIT039 patch application period and for 7 days afterwards; 5) women having no possibility of being pregnant and satisfying one of the following conditions, i.e., in menopause, with 12 months or more having passed since the last menstruation without pathological reason, and having undergone permanent contraceptive surgery in the past, such as bilateral oophorectomy and bilateral ligation of the fallopian tubes; and 6) be willing to participate in the study and provide written informed consent.

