**Table 1 Tab1:**
[figure not shown]
Study schedule

*ICDRG* International Contact Dermatitis Research Group

The primary endpoint of efficacy is resolution of the treated wart, which will be evaluated by the investigators. The safety endpoint is the incidence of adverse events and adverse drug reactions. Adverse skin reactions are graded according to the criteria of the International Contact Dermatitis Research Group (ICRDG).

The secondary endpoints are as follows: change in the dimension of the treated wart, change in the cross-sectional area (CSA) of the treated wart, and change in the number of clots within the area of the treated wart lesion. These parameters are calculated based on pictures created by the digital camera dermatoscopic system (Fig. 2).

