### Data analysis

All efficacy endpoints are assessed for both the full analysis set based on the intention-to-treat principle and the per-protocol set. The full analysis set includes all patients who receive study treatment and who satisfy study inclusion criteria. The per-protocol set includes all patients who receive study treatment for more than 216 h, who adhere to the study protocol, and who do not receive cryotherapy for their target wart prior to day 54. Exact Clopper-Pearson 80% CIs [17] which correspond to a one-sided significance level of 0.10 are calculated with respect to the efficacy primary endpoint of the disappearance of warts for each arm of the study. The remaining efficacy analyses with 95% CIs are considered to be exploratory and are not adjusted for multiple testing. For patients who drop out of this trial regarding the efficacy primary endpoint of disappearance of warts in the efficacy primary analysis, the missing data are imputed as the failure of disappearance of warts (baseline observation carried forward approach). For the other efficacy analyses, missing data are not imputed. The safety endpoint is the incidence of adverse events and adverse drug reactions, assessed for the safety population that included patients who received any study treatment, and summarized by frequency count and percentage. All analyses are performed with the use of SAS statistical software, version 9.4 (SAS Institute, Cary, NC, USA).

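### The clot endpoint is a ratio to the day-1 count, so it has no value for an eligible wart that shows no clots on day 1

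*Protocol article*

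**What the plan says.** All references are to the protocol article.

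- **Measurements, endpoint list:** one of three secondary endpoints is "change in the number of clots within the area of the treated wart lesion". No restriction to a type of wart is attached to it there.
- **Measurements, text below Fig. 2:** the change is "number of clots on a subsequent day) / (number of clots on day 1", expressed as a percentage. The counts are of "small blood clots within the area of the wart lesion in some warts, especially of the palmer and plantar type". Two dermatologists who do not know the allocation make them by hand.
- **Inclusion criteria:** the target wart qualifies by "having verruca vulgaris measuring 4 to 10 mm on the major axis on the extremities, including the palms and soles". There is no minimum clot count.
- **Data analysis:** "All efficacy endpoints are assessed for both the full analysis set based on the intention-to-treat principle and the per-protocol set". Also: "For the other efficacy analyses, missing data are not imputed". Efficacy analyses other than the primary one are exploratory, with 95% confidence intervals and no multiplicity adjustment.
- **Assignment of intervention:** randomisation is stratified by institution and by hand or foot, not by presence of clots.

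The article gives no rule for a day-1 count of zero and names no clot-positive subset for this endpoint.

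**The concern.** The formula divides by a number that the article itself leads one to expect will be zero in some patients. For those patients the endpoint cannot be calculated at any later visit, which conflicts with assessing it in the full analysis set. The written rules supply no substitute value. The comparison would then rest on a smaller group weighted towards palmar and plantar warts, of a size nobody has planned for.

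There is a second, lesser weakness. Where the ratio is defined but the day-1 count is small, one clot more or less produces a very large percentage change, so equal absolute changes receive very different scores.

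The clot count is worth defining well. It is read by assessors who do not know the allocation, whereas the primary endpoint is judged by investigators who, according to Study design, could tell the patches apart on careful comparison.

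**Working it through.** The plan states no figure for this endpoint. Its only design figure, 44 patients for 80% power, belongs to the primary endpoint and has no bearing here.

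**Step 1: the ratio at different day-1 counts.** Formula from Measurements: later count / day-1 count × 100%. The absolute change (later count minus day-1 count) is shown for comparison.

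| Day 1 | Later | Protocol ratio | Absolute change |
|---|---|---|---|
| 0 | 0 | undefined | 0 |
| 0 | 3 | undefined | +3 |
| 1 | 0 | 0% | −1 |
| 1 | 2 | 200% | +1 |
| 1 | 3 | 300% | +2 |
| 5 | 3 | 60% | −2 |
| 10 | 11 | 110% | +1 |

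The absolute change exists in every row; the ratio does not exist in the first two. The rows 1 to 2 and 10 to 11 are the same change of one clot, scored 200% and 110%.

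**Step 2: can a zero day-1 count occur?** Yes, on the article's own words. Clots are described as a feature of some warts, and eligible sites are "on the extremities, including the palms and soles", so palms and soles are included but are not the only sites. No criterion screens out clot-free warts.

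**Step 3: how many patients would have no value?** The article does not give the share of clot-free warts, so this is a range over an assumed share f. With N = 44 (Study design):

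- patients without a value = 44 × f
- patients remaining = 44 × (1 − f)
- standard error relative to all 44 = √(1 / (1 − f)), assuming equal variance, no other losses, and the same proportional loss in both arms

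| Assumed f | Without a value | Remaining | SE factor |
|---|---|---|---|
| 10% | 4.4, about 4 | about 40 | 1.05 |
| 30% | 13.2, about 13 | about 31 | 1.20 |
| 50% | 22 | 22 | 1.41 |
| 70% | 30.8, about 31 | about 13 | 1.83 |

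The SE factor treats clot-free warts as being as informative as the others. A wart that starts at zero cannot show a fall, so the factor overstates the loss if clot clearance is the only interest.

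**Step 4: do the other two ratios share the problem?** No. An eligible wart measures 4 to 10 mm on its major axis, so its day-1 dimensions and cross-sectional area are positive.

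**The case against.** The strongest reply is that the definition already limits the endpoint: it speaks of "number of small blood clots within the area of the wart lesion in some warts, especially of the palmer and plantar type", which can be read as covering only clot-bearing warts, with the zero case left to the statistical analysis plan. This has some force, and the restriction may be what was meant. But no such subset is defined, the endpoint list carries no limit, and Data analysis places all efficacy endpoints in the full analysis set. The formula is stated outright, so the difficulty lies in a rule that fails for eligible patients rather than in an omitted detail. Even under the limiting reading, clot-free warts have no value.

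A second reply is that a zero count is observed, not missing, so the sentence on imputation does not strictly apply. That stands. That these patients drop out is an inference: the ratio has no value and the article offers no alternative.

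Several stronger readings are tempting and are not supported:

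- **That new clots go unrecorded.** Images are taken on days 1, 8, 15, 29, 43 and 57, and the clots are counted by hand. Clots that appear later can be counted; they only fail to enter the ratio.
- **That the treatment comparison is biased by selection.** The excluded group is defined by a feature present before treatment, so this is not post-randomisation selection. Stratifying by hand or foot gives some protection for balance, though not full protection, because clot presence is not itself a stratum.
- **That a few low-count warts would drive the arm averages.** The article names no mean, model or test for this endpoint; a median or rank summary would fit its text equally well.

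**Conclusion.** The point holds as a defect in a stated definition. The clot ratio is undefined for any target wart with no clots on day 1, the article's own description makes such warts likely, and this cannot be squared with assessment in the full analysis set. Where the day-1 count is small, the ratio is defined but unstable.

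The consequence is limited. The endpoint is secondary and exploratory, and the sample size does not depend on it. What is lost is precision, and generalisability beyond clot-bearing warts. The amount cannot be computed from the article: the range of about 4 to 31 of 44 patients without a value rests wholly on the assumed clot-free share of 10% to 70%. The undefined ratio itself needs no assumption. The change is worth making before analysis, and it does not touch the primary endpoint.

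**What to change.** Redefine the clot endpoint as the follow-up clot count, or the absolute change, compared between arms in all patients with images. Use the day-1 count as a covariate, in a form that is defined at zero, and hand/foot location as a factor. A count model or a rank analysis of covariance would serve. Report the percentage of the day-1 count only as description, in warts with at least one clot on day 1, and give the number of such warts per arm.

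The cost is a change of wording in the protocol or analysis plan. The counts are already to be collected, and no visit, image or reading is added. The result is slightly less simple to present than a single percentage.

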### Assessment of adverse events

Evaluations of systemic or cutaneous adverse events will be assessed throughout the entire course of the study. Cutaneous adverse events are evaluated in accordance with the scoring system proposed by the ICDRG, as summarized in Table 2 [16].

**Table 2 Tab2:** Scoring of cutaneous adverse events

Reaction	Scale
No reaction	–
Erythema only (doubtful reaction)	+?
Erythema with infiltration and papules	+
Erythema with edema, papules, and vesicles	++
Formation of bulla(e)	+++
Irritant reaction^a^	IR

^a^Irritant reactions (IR) tend to form a sharply demarcated area, in contrast to a spreading response in allergic reactions, and tend to disappear within several days once the irritating substance is removed

All adverse events will be reported to the data center and handled in accordance with regulatory requirements.

### Data analysis

All efficacy endpoints are assessed for both the full analysis set based on the intention-to-treat principle and the per-protocol set. The full analysis set includes all patients who receive study treatment and who satisfy study inclusion criteria. The per-protocol set includes all patients who receive study treatment for more than 216 h, who adhere to the study protocol, and who do not receive cryotherapy for their target wart prior to day 54. Exact Clopper-Pearson 80% CIs [17] which correspond to a one-sided significance level of 0.10 are calculated with respect to the efficacy primary endpoint of the disappearance of warts for each arm of the study. The remaining efficacy analyses with 95% CIs are considered to be exploratory and are not adjusted for multiple testing. For patients who drop out of this trial regarding the efficacy primary endpoint of disappearance of warts in the efficacy primary analysis, the missing data are imputed as the failure of disappearance of warts (baseline observation carried forward approach). For the other efficacy analyses, missing data are not imputed. The safety endpoint is the incidence of adverse events and adverse drug reactions, assessed for the safety population that included patients who received any study treatment, and summarized by frequency count and percentage. All analyses are performed with the use of SAS statistical software, version 9.4 (SAS Institute, Cary, NC, USA).

### Sample size

The efficacy primary endpoint is the proportion of subjects with resolution of the treated warts as evaluated by the investigators. The Fisher’s exact test is planned at a one-sided significance level of 0.10. A sample size of 44 randomly assigned patients is set to achieve 80% power with consideration for patients who drop out of this trial or who fail to include the full analysis set under the assumption of at least 55% [18–21] disappearance of warts in the FIT039 group compared with a 15% [22] disappearance of warts in the placebo group. A trial with a two-sided significance level of 5% achieving 80% power was not feasible in terms of the required sample size in this phase I/II clinical trial. Therefore, this study was designed to test a hypothesis with a higher significance level, taking into account a reasonable time frame.

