## Methods and design

### Study design

This study is a multi-institutional, single-blind, placebo-controlled randomized phase I/II clinical trial. A total of 44 adults will be enrolled after they provide written informed consent. Participants will be randomly allocated into FIT039 patch or placebo groups in a 1:1 ratio, and will be blinded as to which agent they receive. The target warts of the participants in the FIT039 group will be treated with conventional liquid nitrogen cryotherapy followed by FIT039 patch application for 14 days, with evaluation of the effect of FIT039 for 56 days. The participants in the placebo group will be treated and evaluated the same as those in the FIT039 group except that a placebo patch will be applied. The study is a single-blind trial since the FIT039 patch is distinguishable from the placebo patch by careful comparison for the investigators. The scheme of this study is summarized in Fig. 1. The study was approved by the institutional review board (IRB) at Kyoto University Hospital on 18 October 2017 (K037, protocol version 1.0, September 2017) and the National Hospital Organization Kyoto Medical Center on 22 November 2017. Any protocol modification will be approved by the IRBs before its implementation. This study will be conducted in compliance with the study protocol, the Helsinki declaration [15] and the Ministerial Ordinance on Good Clinical Practice (GCP) for Drugs. This study was registered with the UMIN Clinical Trials Registry as UMIN000029695 (https://upload.umin.ac.jp/cgi-open-bin/ctr_e/ctr_view.cgi?recptno=R000033930).

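### Cheap improvement, not an error: at the same one-sided 0.10 limit, Boschloo's exact test would give more power than the planned Fisher test at 22 per arm

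*Protocol article*

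**What the plan says.** The Sample size section fixes the test and its level: Fisher's "exact test is planned at a one-sided significance level of 0.10". On size it states: "A sample size of 44 randomly assigned patients is set to achieve 80% power". That number already includes an allowance for drop-outs and for patients left out of the main efficacy population. The assumed resolution rates are "at least 55% [18–21] disappearance of warts in the FIT039 group" and, for the comparator, "15% [22] disappearance of warts in the placebo group". The reason for the high level is also given: "A trial with a two-sided significance level of 5% achieving 80% power was not feasible in terms of the required sample size".

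The Study design section gives the allocation: "Participants will be randomly allocated into FIT039 patch or placebo groups in a 1:1 ratio", hence 22 per arm. The Data analysis section counts drop-outs as failures in the primary efficacy analysis. The article gives no drop-out rate and names no other test for the primary comparison.

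**The concern.** Fisher's test conditions on the total number of resolved warts. With small arms, few tables are possible for each total, so the p-value moves in large steps and the test usually stops well short of its nominal level. Here the sponsor openly accepts a 10% one-sided error rate because the trial must stay small. If the test can spend only part of that 10%, the trial states the full concession and receives only part of the power. An exact test that does not condition on the total can come closer to the limit without exceeding it. What is at stake is some power, mainly if the true effect is smaller than planned or if drop-outs are frequent. Validity is not in question.

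**Working it through.** **Inputs.** From the Sample size section: one-sided level 0.10, rates 0.55 and 0.15, 44 randomised, target power 80%. From Study design: 1:1, so n = 22 per arm. From Data analysis: drop-outs are failures. Assumption: 20% drop-out, because the article states none.

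**Method.** Enumerate every table (x resolved of n on FIT039, y of n on placebo).
- Fisher p-value: P(X ≥ x), with X hypergeometric given the total x + y.
- Power: the sum over rejected tables of Bin(x; n, p1) × Bin(y; n, p2).
- True size: the same sum with p1 = p2 = p, maximised over p.
- Boschloo: use the Fisher p-value only to order the tables, and reject below the largest cut-off for which the maximum size stays at or below 0.10. At 22 per arm that cut-off is a Fisher p-value of 0.155.

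**Step 1: the plan's own figure.** Fisher at one-sided 0.10 has 79.2% power at 16 per arm and 82.5% at 17. Then 17 / (1 − 0.20) = 21.25, rounded up to 22 per arm, or 44. By the other route, 20% drop-outs as failures turn 0.55 and 0.15 into 0.55 × 0.8 = 0.44 and 0.15 × 0.8 = 0.12, and power at 22 per arm is 80.7%. So 44 patients and 80% power reproduce with a drop-out rate of about 20%. With no drop-out, power is 90.1%.

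**Step 2: true size of Fisher at nominal 0.10.**

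| Arms | Maximum size |
|---|---|
| 22 vs 22 | 5.5% (4.7% at a common rate of 15%) |
| 22 vs 21 | 6.4% |
| 19 vs 19 | 7.2% |
| 17 vs 17 | 6.1% |

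**Step 3: Boschloo at the same limit.** At 22 per arm its maximum size is 9.7% (7.4% at a common rate of 15%). It rejects all the tables that Fisher rejects and 16 more, so it cannot have less power. Example: 8 vs 4 resolved of 22 has a Fisher p-value of 0.155 and a Boschloo p-value of 0.097.

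**Step 4: power at 22 per arm, one-sided 0.10.**

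| Scenario | Fisher | Boschloo | Gain (points) |
|---|---|---|---|
| 55% vs 15%, no drop-out | 90.1% | 94.3% | 4.2 |
| 55% vs 15%, 20% drop-outs as failures | 80.7% | 88.0% | 7.3 |
| 45% vs 15%, no drop-out | 73.7% | 82.4% | 8.7 |

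With 17 evaluable per arm and 55% vs 15%, the figures are 82.5% and 89.8%.

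**Step 5: the two-sided 5% design, tested as one-sided 0.025 at 22 per arm.** Fisher has 72.7% power if all 44 are evaluable. Boschloo has 81.7% in that case, 75.4% with 10% drop-outs as failures, and 68.3% with 20%.

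**The case against.** The strongest reply is that nothing here is wrong. Fisher's test is exact and familiar, it holds its level, and the design meets its 80%. That stands, so this is a choice between two defensible tests.

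The unspent error is also not worthless, since it lowers the real false-positive risk. Resolution is judged by investigators, who by the article's own account can tell the patches apart on careful comparison. The tables that Boschloo adds include 3 vs 0, 6 vs 2 and 8 vs 4 resolved, and a cautious sponsor might prefer not to call these positive. This stands as a real cost of the change. But the plan itself sets the tolerance at 10%, and Boschloo stays inside it.

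The larger gain in Step 4 concerns an effect below the planned 55%, for which the trial was not sized. That is fair; at the planned rates the gain is about 4 points without drop-out and about 7 with 20%.

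A reader might infer from the 81.7% in Step 5 that the feasibility sentence is mistaken. The article does not support that. Its 44 is the number randomised, with drop-out allowed for, and 81.7% needs all 44 to be evaluable. With 10% or 20% drop-outs as failures, neither test reaches 80% at that level.

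**Conclusion.** The point holds as a low-cost gain in efficiency. At the stated one-sided 0.10, Boschloo's test has more power than Fisher's at 22 per arm: 4.2 points at the planned rates, 7.3 with an assumed 20% drop-out, and 8.7 if the true FIT039 rate is 45%.

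The figures rest on independent binomial arms of 22, no stratification in the test, and equal drop-out in both arms where drop-out is assumed. A reader might infer that Fisher always wastes about half of the allowed error. That describes only 22 vs 22; one patient fewer in one arm already raises the maximum to 6.4%. Nor is the trial underpowered as planned.

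**What to change.** Before unblinding, state that the primary between-arm comparison of wart resolution uses Boschloo's exact unconditional test at one-sided 0.10, with tables ordered by the one-sided Fisher p-value and the p-value maximised over the common resolution rate. Report Fisher's test as a sensitivity analysis. The feasibility sentence needs no change.

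A mid-p version of the exact test is not a substitute, because it does not guarantee the 10% limit: its maximum size is 10.8% at 16 per arm and 11.5% at 17.

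The cost is a wording change, with no added patients and no change to the endpoint or the level. The downsides are a less familiar test that must be fully specified in advance, and a true false-positive rate nearer to the stated 10%.
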